**Figure 2 F2:**
[figure not shown]
Overview of OPTI-PREM workstreams. BAPM, British Association of Perinatal Medicine; LNU, local neonatal unit; NICU, neonatal intensive care unit; NNRD, National Neonatal Research Database; ODNs, operational delivery network;

Workstream 1: Clinical outcomes study

Workstream 1 aims to determine whether the type (designation) of unit (NICU vs LNU) at birth influences the primary outcome (mortality) and secondary outcomes (morbidities) in babies born at 27–31 weeks gestation.

Workstream 2: study of clinical care provided in different neonatal units

Variation exists in how neonatal units manage preterm babies of all gestational ages, even among units of the same designation.^15–18^ In this workstream, we will address the secondary objective of identifying key differences in unit characteristics and clinical practices that could influence outcome. This will allow us to group neonatal units based on care provided, and to search for associations with gestation specific outcomes, irrespective of their designation.

Workstream 3: cost-effectiveness analysis

The health economics analysis investigates whether being born in settings with an NICU or LNU represent value for money within the National Health Service (NHS). A detailed cost analysis of the neonatal care received will be carried out. An incremental analysis of costs and the number of lives saved between different locations of birth will also be conducted.

Workstream 4: ethnographic study with parents and clinicians

Using an ethnographic approach that accesses their lived experiences^19 20^ of caring for these babies, this stream explores parents' and clinicians’ experiences and perspectives regarding decisions about place of care.

Workstream 5: collaboration with the British Association of Perinatal Medicine (BAPM) to establish framework documents and recommendations on place of birth.

A working group will be established in collaboration with BAPM, which will engage with relevant stakeholders, the BLISS parent advisory panel and other support groups. Its purpose will be to establish a framework document and design recommendations for place of birth for babies born at each week of gestation between 27 and 31 weeks, based on the evidence from this study.

### Workstreams 1 and 3

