Matching to account for measured confounding: We will use matching to construct a balanced sample of babies who were born in NICU or LNU based on observed characteristics, assuming that these groups do not differ in relevant unobservable characteristics so that the differences in outcomes between them may be attributed to the location of birth. We will use propensity scores (PS), which are predicted probabilities of the relevant observed covariates that would be expected to be equal for both groups if the conditional distribution is independent of whether the baby is born in an NICU or LNU.^23 24^ To compute the PS, a logistic model for place of birth will be fitted (LNU vs NICU). The independent variables will include a priori decided set of variables on the basis of expert and clinician input and/or variables associated with the type of unit at the place of birth. Based on previous literature^25 26^ and the data availability in NNRD, we will evaluate a relatively large number of covariates for this model including: gestational age, birth weight, sex of the baby, mothers’ ethnicity, use of antenatal steroids, 5 min Apgar score, deprivation, temperature at birth, maternal medical problems prior to this pregnancy and problems encountered during pregnancy. The selected variables are expected to influence either the place of birth or babies’ outcomes, but none of them would be expected to be influenced by whether the baby is born in an NICU or LNU as they are defined at baseline prior to or immediately after the birth. We believe that the model developed in the above steps will produce the PS given the observed set of covariates to produce balanced groups for the analyses; this means that babies who were born in NICUs and those who were born in LNUs with equal PS will have the same distributions of the observed covariates. After the PS is computed from the model, a matched sample will be created and the covariates will be compared between the groups in the matched sample to examine whether the balance has been achieved or not. If the sufficient balance is not achieved, the PS model will be modified and balance will be reassessed. We will investigate the range of estimated PS for both NICU and LNU babies to identify the region of common support. If there is no comparable NICU baby found in the LNU group, the analyses would produce biassed estimates by matching LNU babies with NICU babies with different characteristics. Therefore, observations not under common support should be dropped from the matching, but we will describe the characteristics of these babies in descriptive statistics. It is difficult to define the size of this matched sample at this stage. The sample size will be affected by how relevant it will be considered to the general population and will be reviewed by the study team. If required, other matching methods will also be applied, such as Mahalanobis distance matching and genetic matching.^27^

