
IVs to account for unmeasured confounding: Since matching is based on the assumption that the place of birth is independent of the potential outcomes conditional on the matching variables (also known as measured confounding). This requires that variables that affect both outcomes and the place of birth are observed and controlled in the matching algorithm. In our case, after matching the babies who were born in NICU or LNU on the basis of observed characteristics, it is possible that unobserved confounding variables still remain unbalanced between the two groups and the matching would result in biassed estimates of the effects of being born in NICU compared with LNU. Although we believe that the richness of our dataset makes the assumptions behind the matching plausible, we will complement our analyses using IVs.^28^ We will explore two-stage least squared regression (2SLS) models with exclusion restrictions that help us to explain variation in the types of unit the babies were born that is independent of outcomes. In the first stage, we will estimate the probability of a baby’s birth in NICU as a function of baby-level characteristics and IVs. The estimated probability of being born in an NICU will then be used in a second equation to estimate the effect of being born in an NICU on the outcomes of interest after controlling for a vector of observed baby-level characteristics. If the IVs are correct, the 2SLS method will generate unbiased estimates of the place of birth on babies’ outcomes.

In general, a variable is considered to be an IV, if it is (1) associated with the type of unit at birth (NICU vs LNU), (2) does not have direct effect on the outcome (say mortality) and (3) is independent of unmeasured confounders (UCs) but may be related to the measured confounders (MCs).^28 29^ The assumed relation of (IV) with outcome (4), type of unit at birth (NICU vs LNU), UCs and MCs can be described by the graph in figure 3.^30^

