Adjusting for heterogeneity within the types of units studied: Using NNRD data and augmented with novel evaluation of the quality of care provided in neonatal units through a PhD project, other parameters such as associations with volume and calibre of work undertaken, medical and nursing staffing, and comparisons against national neonatal auditable standards (using variables such as normal temperature measured within the first hour of life, receipt of breast milk on discharge, parental consultation within the first 24 hours, parent presence on ward round, blood stream infections, among others), will be explored in workstream 2. This information, along with information about the population of babies which are cared for at their unit (but not including outcomes), will be used to undertake a cluster analysis. This analysis will provide groups of units which are similar in terms of their characteristics and the care they provide, irrespective of their designation. The identified variables will be assessed in two ways:

They will be incorporated into workstream 1 as confounding variables to analyse potential heterogeneity between units, and to investigate to what extent they help to explain this.They will be used independently, in isolation and conjunction, to investigate associations with gestation-specific outcomes.

### Workstream 4

Understanding parent and clinician perspectives on decisions about place of care: Observations will explore: (1) factors that parents think should guide decision-making about place of care for babies, and how this happens in practice, (2) clinicians’ perspectives and practices around decision-making about place of care, (3) the impact on parents and families of this decision, and subsequent changes in care location and (4) how parents can best be supported.

Periods of observation within neonatal units will be completed, along with interviews with both clinicians and parents. An experienced qualitative researcher will observe relevant discussions and interactions that take place between parents and clinicians regarding place of care. Observations will be guided by an observation framework, developed through discussions with the project team and project parent panel. The observer will take written notes unobtrusively and will then debrief these either alone or with another member of the team. These debrief sessions will be audio recorded and transcribed.

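### The propensity score may match on 5-minute Apgar and temperature on the premise that place of birth cannot affect them; the article contradicts this for temperature, and timing makes it doubtful for Apgar

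*Protocol article*

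**What the plan says.** Workstream 1 takes unit type at birth as the exposure: "Workstream 1 aims to determine whether the type (designation) of unit (NICU vs LNU) at birth influences the primary outcome (mortality" (the sentence goes on to the secondary outcomes). Under 'Matching to account for measured confounding', the article says that after matching "the differences in outcomes between them may be attributed to the location of birth", which is a claim about the total effect of place of birth.

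The same paragraph introduces the propensity-score covariates with "we will evaluate a relatively large number of covariates for this model including", and the list contains "use of antenatal steroids, 5 min Apgar score, deprivation, temperature at birth". It defends the list by stating that "none of them would be expected to be influenced by whether the baby is born in an NICU or LNU", and gives the reason: "as they are defined at baseline prior to or immediately after the birth".

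Workstream 2, under 'Adjusting for heterogeneity within the types of units studied', names "normal temperature measured within the first hour of life" among the auditable standards against which units are compared. Under 'Data sources', the only temperature item named for the database is the admission temperature, grouped with the admission-related data.

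The instrumental-variable analysis estimates the effect of NICU birth "after controlling for a vector of observed baby-level characteristics"; these characteristics are not itemised.

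**The concern.** A covariate that the exposure can change is not a baseline covariate. The 5-minute Apgar is scored after the birth hospital's team has begun care, and a temperature taken at or near admission follows that hospital's thermal care. If NICU and LNU births differ in early care, matching on its results compares only babies who came through it in the same state. The part of the mortality difference that early care produced then disappears from the estimate.

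There is a second route to bias. Unmeasured severity plausibly affects both early condition and death, so conditioning on early condition can create an association between unit type and severity that was not there before.

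The planned balance check cannot reveal either problem, because it treats equality on these variables as success. The stakes are practical. The Background says that if key outcomes do not differ significantly, cost-effectiveness and family satisfaction should decide where care is delivered, so hiding a real difference would steer the recommendations. Workstream 3 follows the same analytic approach and would inherit the problem.

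**Working it through.** **Text.** The exposure begins at birth. The stated reason for calling the covariates unaffected admits values taken just after birth, that is, after exposure has begun. For temperature, the article elsewhere uses a first-hour reading to judge unit care, so it cannot also presume that temperature is unaffected by unit type. For Apgar, the article says nothing further and only the timing argument applies.

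**Figures in the plan.** The article gives about 6,000 babies a year over five years: 6,000 × 5 = 30,000, as stated. It expects about 5% mortality. It gives no effect size or frequency of poor early condition, so everything below is illustrative. All inputs except roughly 5% mortality are assumptions.

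**A. Mediation only, no confounding.** Let p0 and p1 be the proportions in poor early condition after LNU and NICU birth, R the mortality risk ratio for that condition, d the direct NICU risk ratio, and p̄ = (p0 + p1)/2 (equal groups assumed).
- Base risk b = 0.05/(1 − p0 + p0·R), so that LNU mortality is 5%.
- NICU mortality = b·d·(1 − p1 + p1·R).
- Matched difference = b·(d − 1)·(1 − p̄ + p̄·R).

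With p0 = 0.20, p1 = 0.15, R = 2, d = 0.9: b = 0.05/1.20 = 0.04167; NICU mortality = 0.04167 × 0.9 × 1.15 = 0.0431; total difference = −0.69 percentage points. With p̄ = 0.175, the matched difference = 0.04167 × (−0.1) × 1.175 = −0.49 points. Matching removes 1 − 0.49/0.69 = 29%.

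Over p1 from 0.10 to 0.18 and R from 1.5 to 3, the share removed runs from 8% to 59% when d = 0.9. It is 100% when d = 1 (total −0.05 to −0.71 points, matched 0). If p1 = p0, nothing is removed.

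**B. Collider path.** Let 20% of babies carry an unmeasured severity factor U, independent of place of birth. P(poor condition) = 0.12 + 0.05 (if LNU) + 0.35U; P(death) = 0.03 + 0.08U + β (if poor condition).
- β = 0: the true effect is 0, and the adjusted difference is about +0.1 points.
- β = 0.05: the true effect is 0.05 × (−0.05) = −0.25 points, and the adjusted difference is again about +0.1 points.

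The bias therefore need not be simple attenuation.

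**C. Severity also drives NICU birth.** Let U be standard normal, Z = 1 for NICU birth, A = poor early condition; logit P(Z = 1) = cU; logit P(A) = −1.6 + mZ + U; logit P(death) = −3.75 + 1.2A + 0.8U + dZ, where d is now a log-odds effect. LNU mortality is 4.9%. Numerical integration over U gives risk differences in percentage points:

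| c | m | d | True | A omitted | A adjusted |
|---|---|---|---|---|---|
| 0 | −0.5 | −0.1 | −0.88 | −0.88 | −0.18 |
| 0.1 | −0.5 | −0.1 | −0.88 | −0.47 | +0.09 |
| 0.2 | −0.1 | −0.2 | −0.89 | −0.06 | −0.21 |
| 0.3 | −0.1 | −0.2 | −0.89 | +0.33 | +0.05 |

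In the first two rows omission is closer to the truth; in the last two, adjustment is. What decides it is how strongly unit type alters early condition (m) relative to how strongly severity selects babies into NICU birth (c).

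**The case against.** The strongest reply is that Apgar and temperature are proxies for severity in a study whose main threat is selection. The article says that allocation is non-random and that place of booking may partly follow anticipated illness. Table C shows that leaving the proxies out can bias the result more than keeping them. This stands: removing them is a trade-off, not a plain correction.

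Four stronger readings are tempting, and the documents do not support them.
- *The propensity score will adjust for these variables.* They are candidates to be evaluated, and the final model could omit them. What is fixed is the premise on which they are admitted.
- *The instrumental-variable analysis has the same fault.* Its covariates are not itemised, and it is described as a complement to matching. The concern carries over only if these variables enter it.
- *The article contradicts itself on both variables.* It does so only for temperature. Even there, temperature at birth and first-hour temperature are not stated to be the same field, although admission temperature is the only one named for the database.
- *Most of the effect is lost, or its sign reversed.* A fall from −0.88 to −0.18 arises in one assumed scenario with no confounding. It is not an estimate for this study.

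**Conclusion.** The point holds in a limited form. The premise that place of birth is not expected to influence any covariate is contradicted for temperature by the article's own use of early temperature as a measure of unit care, and it is doubtful for 5-minute Apgar on timing. A matched difference attributed wholly to place of birth is therefore not secure as a total effect if either variable is in the score.

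The size and direction of the net bias cannot be derived from the documents. The 8% to 100% range assumes no confounding and no collider path. The bias is nil if unit type does not alter early condition and these variables are not needed to control confounding. Once severity also drives place of birth, the answer turns on quantities that the article does not give. One model cannot settle this; two, each labelled for what it estimates, show how far the conclusion depends on the choice.

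**What to change.** 1. Correct the sentence claiming that no covariate is expected to be influenced by place of birth, and reconcile it with the Workstream 2 use of first-hour temperature. State which temperature field is meant.
2. Estimate the total effect of place of birth with a propensity score restricted to covariates that the birth unit cannot modify, at minimum leaving out temperature.
3. Report beside it a model that adds 5-minute Apgar and temperature, labelled as not estimating the total effect, and discuss any gap between the two as early care, residual confounding or both.
4. If these variables would enter the two-stage least squares covariates, present that analysis with and without them as well. Carry the same pairing into Workstream 3.

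The data are routinely recorded, so the cost is a wording change and one extra model run (one more for the instrumental-variable analysis if item 4 applies). The statistical price is that one of the two models loses a proxy for condition at birth, which is why both should be shown.

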Most ODNs have a defined gestational age cut-off, below which they aim to provide care in an NICU.^3 10^ However, these criteria differ between networks and are often not adhered to. Currently, care pathways for babies born at 27–31 weeks gestation are undefined and their management is spread, often arbitrarily between NICU and LNU. While there is some evidence to suggest that morbidity profiles (based on common major morbidities such as necrotising enterocolitis, retinopathy of prematurity and bronchopulmonary dysplasia) for the total group of babies born at 27–31 weeks gestation^6^ is similar between LNU and NICU, it remains unknown whether location of care and/or birth, makes a difference to gestation-specific outcomes. Our research will determine whether the type of neonatal unit in the hospital of birth influences outcomes for babies born at 27–31 weeks gestation, and if so, at which set point within this gestational age range care can equitably be provided in either LNU or NICU.

Presently, most pregnant women who want a hospital birth are advised to choose antenatal care and delivery in a hospital in their area,^11^ which may have NICU, LNU or SCBU facilities. With the advent of Choose and Book,^12^ this may be changing. Place of booking may also partly be determined by the anticipated degree of illness or complexity of care required for either mother or baby, if that can be predicted. However, for most women at the time of booking for pregnancy care, these risks are unknown and unpredictable. Women in threatened preterm labour at 27–31 weeks gestation will generally attend their hospital of booking for assessment or one closest to them at the time. Many will, therefore, deliver there, regardless of the type of neonatal care that can be offered. Babies that are inevitably born into an SCBU setting in this gestational age range are usually transferred ex-utero to an LNU or NICU for ongoing care. They may be returned to an SCBU from an NICU or LNU for ‘step-down’ hospital care if this is the unit closest to the mother’s home, they are usually older than 32 weeks gestation and better, but not yet ready for discharge home. Generally, transfers that do occur between hospitals, whether for a mother before delivery or for her baby after birth, and are determined by care requirements, and by cot capacity and adequacy of neonatal nurse and medical staffing.

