The total healthcare, social and education costs associated to prematurity at 27–31 weeks gestation during childhood has been estimated to be £607 million in 2016.^13^ Survival in preterm babies has improved in recent years, and hospital costs are high. With neonatal intensive care averaging £1445 per day and high dependency care £925 per day^14^ in 2017/2018, it is important to ensure that care for less sick preterm babies is not unnecessarily located within an NICU, and that sicker preterm babies are not undersupported in an LNU, potentially resulting in prolonged intensive care and greater short-term and long-term morbidity. Importantly, if key clinical outcomes do not significantly differ between LNU and NICU, then cost-effectiveness and family satisfaction should be the major drivers for how and where health services are delivered.

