**Figure 3 F3:**
[figure not shown]
Diagram of a valid instrumental variable (IV). NICU, neonatal intensive care unit.

A potential IV, used in previous studies in the USA,^26 30^ is the difference of the distances of the mother residential postal code to the nearest NICU and LNU postal codes (excess distance). This has the potential to be an appropriate IV because of:

(1) Association with delivery in NICUs (refers to the arrow from IV to NICU in figure 3). Previous studies suggest that a high-risk mother is more likely to deliver in NICU if she is living close to an NICU hospital.^26^

(2) No direct effect on outcomes (refers to the crossed line from IV to outcome in figure 3). The assumption that the difference in travel times to either facility should not directly affect the outcomes except through the route of whether the baby is born in an NICU hospital,^29^ (3) independence of unmeasured confounding factors (refers to the crossed line from IV to UC in figure 3). This is based on the assumption that mothers do not choose where to live based on distance to a high-level NICU, since preterm delivery is usually not expected before pregnancy. However, because hospitals with NICUs tend to locate in select areas (ie, cities), mothers who live here may be different from those who do not, in terms of socioeconomic characteristics. We attempt to address this issue by controlling for mothers’ occupation and deprivation.

Analysing healthcare costs and cost-effectiveness outcomes: A cost analysis with a UK NHS perspective will be conducted. The cost of neonatal care received by preterm babies in NICU and LNU up to hospital discharge will be estimated. Standard care package in neonatal units will be costed by level of care, as categorised by the six Healthcare Resource Groups (HRG) as listed in table 1. HRGs are defined to group the use of healthcare resources of clinically similar treatments for costing purposes, and each of them is attached a unit cost that gives the average cost to the NHS of providing defined services to NHS patients in England. Unit costs used in our economic evaluation will be extracted from the NHS Reference Costs 2017/2018.

**Table 1 T1:** Reference cost for neonatal critical care—year 2017/2018—NHS England^14^

HRG codes	Types of care	National average unit cost (2017–2018)
XA01Z	Neonatal critical care, intensive care	£1445
XA02Z	Neonatal critical care, high dependency care	£925

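### Even with a fully valid distance instrument, 2SLS estimates the effect in babies whose birthplace responds to distance, not, as the plan states, the effect of place of birth in general

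*Protocol article*

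**What the plan says.** The IV paragraph is in the protocol article under Workstreams 1 and 3, Statistical methods. Matching is used for measured confounding, and because unmeasured confounding may remain, "we will complement our analyses using IVs". The plan then claims: "If the IVs are correct, the 2SLS method will generate unbiased estimates of the place of birth on babies’ outcomes".

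The next paragraph defines a valid instrument. It must be "associated with the type of unit at birth (NICU vs LNU"), must have no direct effect on the outcome, and "is independent of unmeasured confounders (UCs) but may be related to the measured confounders (MCs"). The candidate instrument, described after Figure 3, "is the difference of the distances of the mother residential postal code to the nearest NICU and LNU postal codes (excess distance"). The text there defends it on those three conditions only. Monotonicity, a constant effect and a restricted target group are not mentioned.

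Three other places bear on this:

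- The Abstract asks for the effect of NICU versus LNU care at each gestational week.
- Background and rationale separates less sick babies, who may not need an NICU, from sicker ones, and wants to ensure that "sicker preterm babies are not undersupported in an LNU, potentially resulting in prolonged intensive care and greater short-term and long-term morbidity".
- Background and rationale also says: "Place of booking may also partly be determined by the anticipated degree of illness or complexity of care required for either mother or baby". It adds that transfers, including those of mothers before delivery, follow care needs as well as cot capacity and staffing.

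**The concern.** The quoted sentence gives 2SLS a property that it has only under a further assumption. The three listed conditions do not identify an average effect of place of birth when the effect varies between babies. The plan's rationale allows such variation, both by gestational week and by how sick the baby is. Estimating week by week deals with variation across weeks but not with variation by severity within a week.

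Two interpretations are at stake. First, IV is brought in because matching may leave confounding. If the two methods disagree, confounding is the only explanation that the text offers, and a difference in the babies being described is not considered. Second, the same methods serve the cost-effectiveness workstream. The rationale says that if key outcomes do not differ, cost-effectiveness and family satisfaction should be the main drivers of where care is given. A 2SLS estimate read as covering all babies could enter that reasoning, the lives-saved measure and the week-specific recommendations with a wider scope than it has.

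**Working it through.** **The plan's own figure.** About 6000 babies a year over five years: 6000 × 5 = 30 000, as stated. The plan gives no effect size or power in this article, so there is nothing further to reproduce.

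**Algebra.** Take a near/far contrast of excess distance as a binary instrument Z that meets all three stated conditions. Covariates are left out for clarity. Let D be birth in an NICU and Y death before discharge. Split the babies into those born in an NICU at either distance (share a, effect τa), those whose unit of birth changes with distance (share c, effect τc), and those born in an LNU at either distance (share l, effect τl), with a + c + l = 1.

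- Effect in all babies: a·τa + c·τc + l·τl.
- 2SLS target: [E(Y|Z=1) − E(Y|Z=0)] / [E(D|Z=1) − E(D|Z=0)] = c·τc / c = τc.
- Discrepancy: τc − (a·τa + c·τc + l·τl) = a(τc − τa) + l(τc − τl).

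The discrepancy is zero if the effect does not vary with response to distance. Otherwise it depends on shares and effects that the document does not give.

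This result already assumes monotonicity. If a share f with effect τf moved the opposite way, the target would be (c·τc − f·τf)/(c − f), which need not be an average of effects in anyone. With continuous distance, as planned, τc becomes a weighted average over distance-responsive babies. The other two groups still get no weight.

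**Numerical illustration.** From the document: n = 30 000 and mortality of about 5%. Assumed, because the document gives no values: a continuous valid instrument; 10% to 30% of babies born in an NICU whatever the distance; baseline risk of 15% in them; a benefit of 3 or 6 percentage points in them; no effect in the others. There were 300 replicates per scenario.

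- With a 20% share and a 6-point benefit, the true average is 0.20 × (−6) = −1.20 points. Risk in the other babies is (0.05 − 0.20 × 0.09)/0.80 = 4.0%. Mean 2SLS was −0.02 points (SE 0.65).
- Over all six scenarios the true average runs from 0.10 × (−3) = −0.3 to 0.30 × (−6) = −1.8 points. Mean 2SLS stayed between −0.04 and +0.01 points.
- With the same effect in every baby, a true −1.2 gave −1.18 and a true −0.6 gave −0.58.

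So 2SLS recovers the overall effect under homogeneity and misses it when the effect varies with response to distance. The heterogeneous scenarios are extreme by design. They show the mechanism and do not forecast this study.

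**The case against.** The sentence is conditional, distance is only called a potential instrument, and 2SLS complements matching, whose assumptions the plan calls plausible. All true, but the conditional does not rescue the claim, because the gap remains when the instrument is fully correct.

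A reader might go further and infer that the sickest babies reach an NICU whatever the distance and so drop out of the comparison. The document does not say this. Background and rationale says that for most women risk cannot be foreseen at booking. It also says that women in threatened preterm labour generally go to their booked or nearest hospital and that many deliver there whatever neonatal care it offers. The text after Figure 3 says that living near an NICU makes a high-risk mother more likely to deliver in one, so many high-risk babies are probably distance-responsive. The worry about sicker babies in LNUs also concerns babies who can be born in an LNU, and these are not the always-NICU group.

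A reader might also infer that a null 2SLS result would override matching. No rule in the article says so.

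Large losses of power can be simulated, but they follow from what is assumed. If 20% of babies always go to an NICU and carry the whole of an average effect of −1.5 points, their own effect must be −1.5/0.20 = −7.5 points. From an assumed 10% baseline that gives 2.5%, below the 4% assumed for lower-risk babies. Setting the effect in responsive babies to zero also forces rejection down to about 5%. Such figures should not be cited as properties of this study.

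Two further points stand in part. Distance-responsive babies may be the relevant group for some place-of-birth policies, but the plan would then need to say that its IV result is about them. The detail of describing that group can sit in a fuller analysis plan, but the incorrect sentence is in this document.

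**Conclusion.** The stated property is too strong as written. Under the three listed conditions and varying effects, 2SLS does not identify the effect of place of birth in all babies. With monotonicity added, it consistently estimates a weighted average effect in distance-responsive babies. The word unbiased is also loose, since 2SLS is consistent and not exactly unbiased in finite samples, but this is minor with about 30 000 babies and a strong first stage.

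The conclusion rests on algebra and on the plan's own allowance that effects may vary. Its size cannot be given. The document makes some always-NICU babies plausible but states neither their share nor the effect in them. What follows is limited: a difference between matching and 2SLS is not, on its own, evidence of unmeasured confounding, and a 2SLS result, null or not, should not be carried to babies whose birthplace does not depend on distance. The matched estimate has its own restricted scope, since babies outside common support are dropped, which is another reason to compare the two on a common profile. This should be corrected, but it does not invalidate the IV analysis.

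**What to change.** Replace the sentence with wording such as:

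> Under conditions (1)–(3) and monotonicity (living relatively nearer an NICU never makes NICU birth less likely), 2SLS consistently estimates a weighted average effect of NICU birth in babies whose place of birth responds to excess distance; it equals the effect in all babies only if the effect does not vary with that response.

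Then add three rules:

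1. Overall and by gestational week, report first-stage strength and the covariate profile of distance-responsive babies beside the whole cohort. Distance is continuous, so a prespecified near/far contrast is one way to define that profile.
2. Before attributing a gap between matching and 2SLS to unmeasured confounding, reweight the matched estimate to that profile and compare it with 2SLS.
3. Limit conclusions from 2SLS, including a null result and any lives-saved figure based on it, to distance-responsive babies.

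The cost is a narrower IV conclusion and one extra reweighted analysis of data already held. No new data are needed.
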